- Assessment of participants' cognitive capacity using the NIH Toolbox® Cognition Battery. Previous evidence suggests that nabilone may cause acute mild decrement in attention and working memory (27). We will use the NIH Toolbox® Cognition Battery, which has been shown as a good candidate outcome measure to examine broad nonverbal cognitive changes for individuals with IDD (valid and reliable for those with a mental age of  $\geq 5$  years; implementable for those with a mental age of  $\geq 3$  years) (42), to assess the baseline attention and working memory.
- Assessment of SBP of participants, including behavioural problems using the ABC-I and Modified Overt Aggression Scale (MOAS), as reported by the caregivers. These scales will be the principal measures for detection of changes in SBP.
- Assessment of anxiety using the parent-rated General Anxiety Subscale of the Anxiety, Depression, and Mood Scale (ADAMS). Nabilone and THC at low doses have been shown to alleviate anxiety, thus this measure is used for exploratory aims to detect a signal of behavioural/mood change with nabilone use.
- Assessment of caregiver's stress and crisis using the Stress Subscale of Depression Anxiety Stress Scales (DASS-21) and Brief Family Distress Scale (BFDS). As SBP cause major caregiver burden, we aim to assess whether the caregiver's stress and distress would improve if nabilone also improves participants' SBP.
- Exploratory assessment of autism symptoms using the Social Communication Questionnaire for Adults with Intellectual Disability (SCQ-AID). Prior evidence suggests that autistic symptoms may be associated with the presentation of SBP (43). We aim to explore whether the baseline autistic symptoms would modulate treatment effects of nabilone.
- Optional assessment of MRI Imaging (dependent on the participant's ability to comply with the following assessments, in the opinion of the carers/parents and investigator).

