- Assessment of adverse events using the UKU side effect rating scale, examined by the researcher or investigator, to systemically investigate the physical AEs of nabilone.
- Re-measuring of vital signs (including blood pressure to check orthostatic hypotension) and weight to monitor the physical AEs of nabilone.
- Re-assessment of participants' cognitive capacity using the NIH Toolbox® Cognition Battery, to monitor any acute cognitive change (AEs) due to nabilone.
- Re-assessment of caregiver rated ABC-I, MOAS, and General Anxiety Subscale of ADAMS. CGI-S and CGI-I will be rated by the investigator to evaluate the severity and improvement of the behavioural problems after nabilone treatment. These re-assessments are implemented to fulfil the exploratory study aim of assessing behavioural changes pre- and post-treatment of nabilone.
- Re-assessment of caregiver's stress and crisis using the Stress Subscale of DASS-21 and BFDS, to investigate changes in their stress and distress after participants takes nabilone.
- Optional re-assessment of MRI Imaging for those who finish the pre-treatment MRI and are willing to receive the second wave of MRI imaging. This is to investigate the change in brain function and structure pre- and post-treatment of nabilone.

Nabilone will be tapered in 0.25 mg daily decrements to prevent acute withdrawal effects. This This proposed down-titration schedule was decided based on a conservative modification from a clinical trial of using Nabilone to treat behavioural and psychological symptoms of dementia (27). Phone calls will be held every other day during the dose-tapering phase, to check whether there are any changes which are believed to be attributed to withdrawal effects. A safety follow-up visit (S-F) will be scheduled after 2 weeks of full discontinuation from the study drug.

The study team will pick up the blister pack from Research Pharmacy, and then distribute to the participant/caregiver. Upon receipt of the nabilone supplies, an inventory will be performed and a receipt log filled out and signed by the research staff who picks up the blister pack. Designated research staff/pharmacy must count and verify that the pickup contains all the items noted in the

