#### Scales to measure cognitive function

NIH Toolbox® Cognition Battery (NIHTB-CB): The NIHTB-CB is an iPad-based battery of brief memory, executive function, processing speed, and language tests, which was developed within the NIH Blueprint for Neuroscience Research. The NIHTB-CB has the potential to provide a highly standardized, objective, and scalable tool for use across laboratories and clinical trial sites and has been shown as a good candidate outcome measure to examine broad nonverbal cognitive changes for individuals with IDD (valid and reliable for those with a mental age of  $\geq 5$  years; implementable for those with a mental age of  $\geq 3$  years) (42). The NIHTB-CB will be used to monitor the change in cognitive performance pre-and post-treatment of nabilone. To allow for accurate scoring based on the established norm, the administration of NIHTB-CB will collect a set of limited personal identification information, including sex, age, and education level, plus study ID. This assessment will be delivered on-site at pre-treatment (V 0), post-treatment (V 1), and safety follow-up (V-F). It takes approximately 60 minutes to complete each full assessment. It should be noted that this administration time is approximate considering the different levels of motivation and cooperativeness in participants. The norming version for neurotypical people aged 3-85 years is intended to be administered with a 30-minute duration (48).

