## **7.2. Stopping of parts of the study**

If participants fail to discontinue the use of any cannabinoids or high doses of benzodiazepine (more than the benzodiazepine equivalent to lorazepam 2 mg daily), psychostimulants for attention-deficit hyperactivity disorder (ADHD), and nonbenzodiazepine hypnotics 4 weeks before the start of the titration phase, they will not progress to the Pre-Treatment visit (V 0). We will discuss with participants and their caregivers to confirm their willingness to further proceed with the study. The participants are only permitted to proceed with the trial when they do not fulfill this exclusion criterion of the concurrent use of other cannabinoids and high dose of benzodiazepine.

If participants cannot, or are unwilling to, comply with the procedures of NIH Toolbox® Cognition Battery, but can comply with the remaining parts of the study, we will stop assessing them using this cognitive battery. These participants will still proceed with the other parts of the entire studies.

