## **9.3. From nabilone**

Nabilone is indicated for severe nausea and vomiting associated with cancer chemotherapy and commercially available in Canada. Its use is usually safe and well tolerated, with sedation (~20%) and dry mouth (~10%) being the most commonly reported adverse events (no side effects of appetite and movement) in elderly with dementia or Parkinson's disease, or people with cancer (26-28, 30, 34). This safety profile is comparable to those reported in studies of CBD (36) and clonidine (37) (one of the medications for SBP of people with developmental disabilities) use in people with IDD, and less substantial relative to antipsychotics.

The addictive potential of nabilone is very low and unlikely (38), for its effect of less euphoria, slower onset of action, and more difficult titration compared to smoking cannabis. Nabilone has been shown to help with sustained abstinence from marijuana (39). The incidence of nabilone

induced full-blown psychotic disorder are also rare, and this propensity is only concerning in people with a personal or family history of schizophrenia, who will be excluded from this study. Although promising, no data ever showing efficacy and safety regarding nabilone in this population have been noted.

Per the product monograph and previous reports issued by the Canadian Agency for Drugs and Technologies in Health (26-28, 30, 34, 35), risks and side effects related to nabilone we are studying include:

- Drowsiness (66.0%)
- Vertigo (58.8%)
- Psychological high (38.8%)
- Dry mouth (21.6%)
- Depression (14.0%)
- Ataxia (reduced body coordination) (12.8%)
- Blurred vision (12.8%)
- Sensation disturbance (12.4%)
- Anorexia (loss of appetite) (7.6%)
- Asthenia (feeling of numbness and tingling) (7.6%)
- Headache (7.2%)
- Orthostatic hypotension (feeling dizzy when standing up) (5.2%)
- Euphoria (4.0%)
- Hallucinations (2.0%).

However, these estimates are influenced by factors such as drug dose, patient characteristics, detection technique, setting, and physician judgments, among others. Consequently, the side effects listed above are presented solely to indicate the relative frequency of adverse events reported in representative controlled clinical studies conducted to evaluate the safety and efficacy of nabilone across different situations.

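### Section 7.2 stops NIH Toolbox testing at any visit for non-compliance, so inability that first appears on nabilone becomes a missing score on a cognitive safety outcome

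*Protocol*

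**What the plan says.** **The stop rule.** Section 7.2 opens with "If participants cannot, or are unwilling to, comply with the procedures of NIH Toolbox® Cognition Battery" and, provided the person can manage the rest of the study, concludes that "we will stop assessing them using this cognitive battery". It adds: "These participants will still proceed with the other parts of the entire studies". It names no visit, asks for no reason, and mentions neither adverse event review nor a further attempt.

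**The purpose of the battery.** Table 1 places the NIH Toolbox under its safety outcomes, at V 0, V 1 and V-F. Section 3.1 says the V 1 repeat is "to monitor any acute cognitive change (AEs) due to nabilone". The same section explains why the battery was chosen: "Previous evidence suggests that nabilone may cause acute mild decrement in attention and working memory".

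**Timing.** V 1 falls at the end of the four-week stable-dose phase, before the taper begins. V-F falls two weeks after full discontinuation. V 1 is therefore the on-drug measurement and V-F the off-drug one.

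**Who can do the test.** Sections 3.1 and 3.4 describe the battery as valid for a mental age of at least 5 years and usable from 3 years. Section 3.4 puts a full session at about 60 minutes.

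**The concern.** Two different situations trigger the same rule. In one, the participant was never able or willing to do the battery. There is no baseline, and stopping loses nothing that could show change. In the other, the participant completed V 0 and then cannot complete V 1 while taking nabilone. That may be the drug effect the V 1 test is there to find, yet the rule turns it into an absent score.

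The rule also reaches forward. If assessment with the battery stops at V 1, the V-F retest is not done either, so there is no record of whether ability returned off drug.

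The primary objective is tolerability and safety, and the next trial is to be designed on these results. If the participants with the clearest cognitive problem are the ones without scores, the battery can look more reassuring than it should. An analysis plan cannot repair this later, because the protocol itself halts the data collection: a retest never attempted and a reason never recorded cannot be reconstructed.

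**Working it through.** The protocol gives no figure for untestability or for Toolbox change, so there is no stated result to reproduce on this point. The check is mainly one of reading; the numbers only show direction and scale.

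**Step 1. Apply the rule to each case.**

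| Participant | V 0 | V 1 (on drug) | V-F (off drug) | Lost under 7.2 |
|---|---|---|---|---|
| Never able or willing | no score | not attempted | not attempted | no change score was possible |
| Able at V 0, newly unable at V 1 through impairment | score | no score | not attempted | on-drug decline and off-drug recovery |
| Able at V 0, refuses at V 1 | score | no score | not attempted | cannot be told apart from the row above unless a reason is recorded |

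**Step 2. Is the second row plausible?** Section 9.3 lists drowsiness at 66.0% and ataxia and blurred vision at 12.8% each; Section 3.4 describes an iPad-based session of about 60 minutes. Failure for drug-related reasons is possible. The protocol gives no rate for it.

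**Step 3. Illustrate the size.** Section 8 expects 40 to enter titration with 25% attrition: 40 × 0.75 = 30. Assume, generously, that all 30 were testable at V 0. Let *k* (assumed) become untestable at V 1 through impairment, and let nobody else decline.

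- Among those still tested: 0/(30 − *k*) impaired, with exact upper 95% limit 1 − 0.025^(1/(30 − *k*)).
- Counting newly impaired participants: *k*/30, with exact 95% interval.
- If each affected participant truly fell by an assumed *D* = 1 to 2 SD: full-group mean change = −*kD*/30, against 0 among those still tested.

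| *k* (assumed) | Still tested: impaired (upper limit) | All 30: impaired (95% CI) | Full-group mean change, *D* = 1 to 2 SD |
|---|---|---|---|
| 1 | 0/29 (11.9%) | 3.3% (0.1 to 17.2%) | −0.03 to −0.07 SD |
| 3 | 0/27 (12.8%) | 10.0% (2.1 to 26.5%) | −0.10 to −0.20 SD |
| 6 | 0/24 (14.2%) | 20.0% (7.7 to 38.6%) | −0.20 to −0.40 SD |

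At *k* = 6 the upper limit from those still tested (14.2%) lies below the proportion affected (20.0%). If fewer were testable at V 0, each loss weighs more: 3 of 20 is 15%.

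**Step 4. Look for another route.** The UKU scale is given at V 1 and V-F (Sections 3.1 and 3.2, Table 1). Section 12 has adverse events assessed at every visit and call, and logged if staff observe them. These can catch overt impairment. No text links a failed battery to either route.

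**The case against.** The strongest reply is that safety capture does not rest on this battery. Someone too drowsy or confused to be tested would be seen by staff, rated on the UKU at the same visit and entered in the log. This stands in large part. A reader might infer that such a participant vanishes from the safety record altogether; the documents do not support that. What is lost is the signal from this instrument, which was added specifically for attention and working memory.

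Second, the rule was probably meant for people who could never do the test, as the mental-age remarks suggest. That is plausible, but the text does not say so. If it was the intent, stating it costs nothing.

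Third, new untestability may be rare. Section 3.1 expects only a mild decrement, Section 9.3 also quotes sedation of about 20% in other populations and cautions that the listed rates depend on dose and setting, and Section 9.1 allows rest breaks and split visits. All of this bears on frequency, which is unknown. It does not change what happens when compliance still fails.

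Three further inferences go too far:

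- *The planned analysis will report no decline.* Section 8 applies paired tests to behavioural and brain changes and describes safety by percentages of adverse effects. It specifies no mean Toolbox change.
- *The bias can only run toward no harm.* The rule also covers unwillingness, in a population selected for severe behavioural problems, so missing scores need not track drug-related decline.
- *Norm-based scoring adds a floor that hides decline.* The protocol gives no floor and does not fix normed scores as the measure of change. A floor would also flatten rises as well as falls.

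**Conclusion.** The point holds for the NIH Toolbox as a safety outcome. As worded, Section 7.2 lets inability that begins on treatment become a missing V 1 score and removes the V-F retest, contrary to the purpose Section 3.1 gives the battery. Its results may then understate cognitive harm.

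The size cannot be stated from the documents. The illustration runs from 1 to 6 of 30 newly untestable, that is 3.3% to 20.0% affected against none seen among those still tested. It assumes that the loss is due to impairment, that all 30 were testable at V 0 and that nobody else declines. Refusals unrelated to the drug would weaken it, as would impairment picked up by the UKU or the log.

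This is a cheap improvement to one instrument. It does not show that the trial's safety monitoring fails.

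**What to change.** Reword Section 7.2 so that the stop rule applies only to participants unable or unwilling to do the battery at V 0. For those who completed V 0:

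1. Attempt the battery at V 1 and again at V-F, subject to the participant's willingness, whatever happened at V 1.
2. Record the reason for any non-completion, separating inability from refusal.
3. Have the investigator review new inability as a possible adverse event. Do not count every non-completion automatically as a cognitive adverse outcome, since that would mislabel refusal.
4. Report the number testable at V 0, V 1 and V-F alongside the scores.

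The cost is a few lines of protocol text and one eCRF field; testing at V 1 and V-F is already scheduled. The downside is that some non-completion unrelated to the drug will be reviewed, which the recorded reason makes visible.

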## **8. SAMPLE SIZE AND DATA ANALYSIS**

To test the Hypotheses 1 and 2, we aim to enroll 40 patients to enter the dose titration phase, consistent with common sample sizes for Phase I trials (63).

We assume the attrition rate of 25% from the dose titration phase to entering the open-label phase. To test behavioural changes at the group level (Exploratory Objective), the sample size of the remaining participants (N=30) could be sufficient to detect differences with effect size Cohen's d as low as of 0.53, and at power = 0.8 and two-sided  $\alpha$ -level = 0.05 (G\*Power 3.1), which is similar to that detected in the study investigating the effects of nabilone on agitation associated with dementia (27).

Paired-t test will be used to investigate the pre- vs. post-treatment behavioural and brain changes. Exploratory analyses will be performed to determine predictors of response including baseline individual features, using logistic regression. Safety profiles will be described in the percentage of each adverse effects. For MRI measures, non-parametric tests will be used to explore the brain changes with nabilone treatment, assuming that only few participants can finish MRI scans eventually.

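### Section 8 names two tests for the same MRI changes and fixes logistic regression where the main outcomes are scale scores; a single arm also cannot show effect modification (minor)

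*Protocol*

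**What the plan says.** Section 8 plans to take 40 people into titration ("we aim to enroll 40 patients to enter the dose titration phase"). It expects a quarter to be lost before the open-label phase ("We assume the attrition rate of 25% from the dose titration phase to entering the open-label phase") and bases the behavioural comparison on the rest: "the sample size of the remaining participants (N=30) could be sufficient to detect differences", with "effect size Cohen's d as low as of 0.53".

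The analysis paragraph then makes three statements that matter here:
- On pre-post comparisons: "Paired-t test will be used to investigate the pre- vs. post-treatment behavioural and brain changes".
- On predictors: "Exploratory analyses will be performed to determine predictors of response including baseline individual features, using logistic regression".
- On imaging, three sentences after the first: "For MRI measures, non-parametric tests will be used to explore the brain changes with nabilone treatment". The reason given is that few participants are expected to finish scanning; no number is stated.

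Section 3.1 names ABC-I and MOAS as the principal measures of change in behaviour, and Table 1 lists ABC-I as the primary clinical effect outcome. On the autism questionnaire (SCQ-AID), Section 3.1 says: "We aim to explore whether the baseline autistic symptoms would modulate treatment effects of nabilone".

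**The concern.** There are three separate issues.

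**Two methods for one endpoint.** The protocol collects no brain measure other than MRI (Section 3.4). The brain part of the paired-t sentence and the later MRI sentence therefore cover the same data with different tests, and nothing says which governs. A reader of the results could not tell which test was the planned one.

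**A binary-outcome model for score outcomes.** Logistic regression needs a yes/no response. If that response is a cut of the ABC-I or MOAS change, the model discards information that the score holds, in a sample of about 30 that has little to spare.

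**A question the design cannot answer.** Whether a baseline feature modifies the effect of nabilone is a comparison of drug effects across levels of that feature, and so needs a comparator. This trial is open-label with one arm, and entry requires an ABC-I score of at least 18 and a CGI-S score of at least 4 (Section 3.3). Change from baseline therefore mixes drug effect with regression to the mean and natural course. A feature that predicts change may be predicting any of these.

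**Working it through.** **The plan's own figure.** 40 × 0.75 = 30. For a two-sided paired t-test at alpha 0.05 and power 0.80, the noncentral-t calculation with n = 30 gives a detectable d of 0.529, and power at d = 0.53 is 0.801. The stated 0.53 is correct and is not in question.

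**MRI tests side by side.** The first sentence assigns behavioural and brain changes to the paired t-test. The fourth assigns brain changes on MRI to unspecified non-parametric tests. The fourth is the more specific and gives a reason, but it does not say that it replaces the first.

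**What a rank test can show with few pairs.** The smallest two-sided p-value of an exact signed-rank test on n pairs is 2/2^n:

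| Pairs | Smallest two-sided p |
|---|---|
| 4 | 2/16 = 0.125 |
| 5 | 2/32 = 0.0625 |
| 6 | 2/64 = 0.031 |
| 8 | 2/256 = 0.0078 |

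With five or fewer pairs, 0.05 is out of reach; from six it is attainable. Simulated power at six pairs is still only about 0.12 for d = 0.53 and 0.35 for d = 1.0.

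**Logistic against linear regression.** Inputs: n = 30 (Section 8), one predictor, two-sided alpha 0.05. The protocol gives neither a predictor-outcome correlation nor a response rate, so 0.4 to 0.5 and 30 to 50% are assumptions. Predictor and change are simulated as bivariate normal, and response is a cut of the change.

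| Assumed correlation | Linear | Linear, adjusted for baseline | Logistic, 30 to 50% responders |
|---|---|---|---|
| 0.5 | about 0.83 | about 0.82 | about 0.62 to 0.68 |
| 0.4 | about 0.60 | about 0.59 | about 0.43 to 0.46 |

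Other runs of the same set-up gave logistic power as low as 0.60 and 0.41, so these figures are good to a few hundredths.

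A hand check of the linear column uses the Fisher transformation, power ≈ Φ(atanh(r)·√(n−3) − 1.96):
- r = 0.5: 0.549 × 5.196 − 1.96 = 0.89, so power is about 0.81.
- r = 0.4: 0.424 × 5.196 − 1.96 = 0.24, so power is about 0.60.

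The loss from cutting the score is therefore about 0.15 to 0.21 in power at correlation 0.5 (0.83 − 0.68 and 0.83 − 0.62), and about 0.14 to 0.17 at 0.4 (0.60 − 0.46 and 0.60 − 0.43).

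**The case against.** The strongest reply is that everything here is exploratory. The primary objective is tolerability and safety, MRI is optional, and no primary conclusion or sample-size figure is touched. That stands, and it sets the severity.

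The MRI sentence, being specific and reasoned, would naturally be read as overriding the general one. That is probably the intention, but the text should say so.

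Response is not tied to ABC-I. It could rest on CGI-I, a seven-point scale whose categories lend themselves to a responder split. The power loss above would then not apply as computed, which is why it is stated conditionally. A CGI-I responder model would still bypass the measures that Section 3.1 calls principal.

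Three stronger readings are tempting, and the protocol does not support them:
- *The MRI test cannot reach significance with the scans expected.* The protocol gives no scan count, names no particular non-parametric test and sets no alpha for MRI; its 0.05 belongs to the behavioural comparison. The limit holds only for an exact two-sided signed-rank or sign test on five or fewer pairs.
- *The responder cut-off will be chosen after seeing the data.* None appears in the protocol, but such a definition is commonly left to the SAP, which is not at hand. Its absence is not a finding.
- *Several predictors cannot be fitted.* At assumed response rates of 20 to 50%, 30 people give 6 to 15 events, or 0.6 to 1.5 predictors at ten events each. That bites only if predictors enter one model together, and Section 8 does not say that they do.

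A last objection is that linear regression is itself not well powered. That is true at a correlation of 0.4 (about 0.60). The change reduces the loss but does not remove the limits of 30 people.

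**Conclusion.** The point holds as a minor one, in three parts. The duplicate test for brain changes is plain on the page and rests on no assumption. The preference for modelling the score is conditional: if response is a cut of a scale score, power with one predictor falls from about 0.60 to 0.83 to about 0.43 to 0.68 under the assumed correlations and response rates, and the baseline-adjusted linear model keeps nearly all of the linear power. The effect-modification aim cannot be met by a single-arm design, whatever the analysis plan says; only association with change can be reported. N = 30 counts people entering the open-label phase, so pairs at V 1 may be fewer and power lower for every model.

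**What to change.** 1. In Section 8, strike *and brain* from the paired-t sentence so that the non-parametric method alone applies to MRI. Add that, with five or fewer paired scans, individual changes are reported descriptively without a test.
2. Replace logistic regression with linear regression of V 1 ABC-I on V 0 ABC-I plus one baseline predictor at a time, SCQ-AID first because Section 3.1 singles it out. Keep any responder analysis as a supplement.
3. In Section 3.1, reword the SCQ-AID aim to ask whether baseline autistic symptoms are *associated with change during nabilone treatment*.

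The cost is a few sentences, with no new data and no change to visits or treatment. The one small downside is that a regression slope is less directly readable than a responder rate, which the supplementary analysis covers.
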